### Data collection

#### Registration and waitlist data collection

When study funding was announced in January 2016, a database (study registry) was established so that individuals could register their interest in the study thereby assisting the study team's plans for study implementation (Table 1). The register collects participants' contact details, previous PrEP use and which study site participants would prefer to attend.

A few days prior to commencement of study enrolment, registered individuals were emailed information on how to book a PrEPX appointment at their preferred study site and information on whether co-payment would likely be required by the clinic at study enrolment. Clinics were provided with a list of individuals planning to attend their clinic, including contact details, if currently using PrEP and if currently a client at that clinic.

The study opened on 26 July 2016 and data collection among enrolled participants is scheduled until July 2019.

As enrolment neared capacity (*n* = 2,600) a waitlist register was established so individuals could register their interest if further places became available. The waitlist register collected the same variables as the initial registry of interest. Consistent with the protocol at study opening, with each release of additional study places registered individuals were emailed details of their preferred study site and clinics were emailed information on their potential PrEPX participants.

#### Participants' baseline and follow-up data collection

The laboratory investigations and surveys that participants undergo at baseline are outlined in Tables 3, **4**. All study participants are evaluated with baseline laboratory tests and the baseline enrolment form survey (Tables 3, 4, respectively). Participants will be offered hepatitis B vaccination as required. Further surveys include a self-reported behavioral survey completed by participants attending five study clinics participating in the Australian Collaboration for Coordinated Enhanced Sentinel Surveillance of Blood Borne Viruses and Sexually Transmitted Infections system (ACCESS, described below), the ACCESS behavioral survey. An in-depth, online survey performed at baseline then 6-monthly thereafter was completed by 1,200 participants at enrolment. This survey provides more detailed information on sexual behavior, adherence, attitudes to PrEP and acceptability of the study. An in-depth, face-to-face interview at baseline and month 21 was completed by up to 30 participants, purposively selected from those completing the in-depth online survey (Table 4).

**Table 4 T4:** Data fields collected in each PrEPX survey.

	**Enrolment form Survey**	**ACCESS behavioral survey**	**In-depth online survey**
**DEMOGRAPHICS**			
Age	X	X	X
Country of birth	X	X	X
Year of arrival	X	X	
Aboriginal and/or Torres Strait islander	X (since 2017)	X	X
Gender identity	X	X	X
Sex assigned at birth	X	X	
Sexuality	X		
Residential postcode			X
Education level			X
**HIV/STI TESTING HISTORY**			
Time since last HIV test	X	X	X
Time since last STI test	X		X
Place of last HIV test		X	
Reason for HIV test		X	
**Sexual Behaviors and Risks**			
Gender and number of sex partners		X	X
Condom use regular and casual partners		X	X
Regular partners/sex/HIV status			X
Other risk reduction with casual partners		X	X
Group sex		X	
Drug use		X	X
Injecting drug use	X	X	X
Sex work		X	X
**PREVIOUS PEP/PrEP**			
Previous PEP use	X		X
Previous PrEP use	X	X	X
Method of acquiring PrEP	X		X
**PrEP ELIGIBILITY ASSESSMENT**			
GBM risk assessment	X		
Hetero risk assessment	X		
Transgender risk assessment	X		
IDU risk assessment	X		
Clinician discretion	X		
**CLINICAL PRESENTATION**			
Acute HIV or STI symptoms	X		
Past medical history	X		
Current medication	X		
**CLINICAL RESULTS**			
eGFR, HIV, HBV, HCV, Pregnancy	X		
**Beliefs about HIV**			X
**Attitudes to PrEP**			X
**Attitudes to HIV treatment and prevention**			X
**Condom use & opinions**			X
**STIs**			X
**Clinic Visit Experience**			X

PrEPX utilizes the ACCESS system to collect HIV, STI and other test information. ACCESS includes primary care, sexual health and pathology services with data primarily collected through the GRHANITE^TM^ data extraction software (47). GRHANITE^TM^ interfaces with clinic patient management systems to extract patient test results, demographics, and prescriptions and with pathology service data systems to extract test results and demographics (47). Test results routinely collected as part of ACCESS include HIV, *Chlamydia trachomatis* (CT), *Neisseria gonorrhoeae* (NG), *Treponema pallidum* (syphilis), hepatitis B virus and, hepatitis C virus. Tests additionally collected for PrEPX include urine protein: creatinine ratio, serum creatinine, and eGFR. GRHANITE^TM^ will be used also to extract data to evaluate whether enrolment in PrEPX is associated with an increase in ancillary health outcome measures including diagnosis and treatment of hypertension, depression and other common medical conditions.

GRHANITE^TM^ data extraction software removes all patient identifying details before data extraction from the clinics or pathology services. Patients are assigned a unique identifier, which allows longitudinal analysis of a patient within a clinic. PrEPX participants are re-identified within ACCESS study sites through matching a numerical identifier, year of birth and enrolment clinic within the enrolment survey and the ACCESS dataset. De-identified test results are stored at the Burnet Institute.

#### Other study data

Clinic staff at three of the four Victorian primary care clinics, two sexual health clinics, and the hospital clinic have been invited to complete a survey about characteristics of their clinic, their PrEP patient load and clinic level challenges experienced during the study at baseline, months 12 and 24.

Pharmacy data including drug accountability logs and participant record logs are manually collected from each participating site.

Victorian HIV diagnosis data will be collected from the Victorian Department of Health and Human Services (DHHS). It is a legal requirement that all newly diagnosed cases of HIV are notified to the DHHS. Notifications include test result data from the laboratory and an enhanced surveillance form from the diagnosing doctor that includes demographics, test history and exposure to HIV. Non-identifiable line listed data will be collected from the Victorian DHHS including the diagnosis date, country of birth, age, and exposure to HIV for all newly diagnosed cases in Victoria between 2013-2019.

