### Study setting

The study is set in Victoria, the second most populous Australian state with a population of 6.2 million people and about 45,000 GBM (2, 39). In 2015, there were 286 new HIV diagnoses in Victoria of which 148 were defined as newly acquired [evidence of diagnosis within 12 months of infection (40)], with diagnosis rates of 4.8 and 2.0 per 100,000 population, respectively (1). In metropolitan Melbourne (the capital of Victoria), where approximately 80% of people newly diagnosed with HIV in Victoria reside (41), PLWH and GBM are cared for by three types of clinics: a small number of general practice clinics that have high caseloads of PLWH and GBM, state-funded sexual health services, and infectious disease (ID) clinics at teaching hospitals. The Alfred Hospital provides a state wide HIV service. These three types of clinics are staffed by general practitioners, sexual health clinicians and infectious disease clinicians who are licensed to prescribe antiretroviral medications on the PBS. Since 2013, the PBS has provided ARVs to PLWH at any CD4 cell count (previously restricted to a CD4 cell count below 500 cells/ml). PrEPX study sites include GBM specialist GP clinics, state-funded sexual health service, the Alfred hospital HIV service, shared care and outreach study sites (Table 1).

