### Sample size estimates

We estimated that there are 300 new HIV infections per year in Victoria based on back-calculation methods applied to surveillance data and a modeling framework. With high and stable testing rates and HIV notification trends in Australia, these estimates have demonstrated strong concordance with actual trends in new infections (1, 48, 49). Approximately 75% of new HIV infections in Victoria occur in GBM, providing an estimate that 225 new infections occur in GBM in Victoria, annually.

We powered the study to avert 68 new HIV infections annually among GBM, which equates to a 30% reduction in new HIV infections in GBM in Victoria. We consider that this would represent a meaningful population-level prevention outcome from scaling up PrEP. Power calculations were based on a HIV incidence estimate of 2.78 per 100 person years (PY) from high risk GBM (consistent with risk criteria guidelines for PrEP) in the Health in Men (HIM) cohort study (50). The HIM study measured HIV incidence among GBM in Sydney in the early-to-mid 2000s (50). There are not adequate, contemporary Victorian data to determine HIV infection risk for GBM, but participants in HIM were not dissimilar in characteristics nor in epidemiological context to GBM in Victoria and Wilson et. al. has shown that the per-capita transmission rate has remained relatively stable since that period (51). We estimated that the number of GBM at risk of HIV in Victoria was 28,846 (225/0.78 per 100PY). With an estimated 24% classified as high risk [as per the HIM study (50)] and hence targeted for study participation, our target population size was therefore estimated as 6,923 (28,846 × 0.24). We estimated that a sample size of 2,600 participants (37% of high risk GBM) was required to achieve the 30% annual HIV infection reduction outlined above. Achieving this PrEP coverage was considered feasible given recent survey data showing that 32% of GBM classified as having high HIV acquisition risk were both willing and eligible to use PrEP (37).

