### Statistical analyses

The study will determine if the provision of PrEP to 2,600 people at high risk of HIV infection in Victoria results in a 30% decline in new HIV infections among GBM over the 36 months of the study. In addition, the study will monitor the rate of new HIV infections in Victoria for a period of 36 months after the PrEPX study commences. Analyses of changes in the rates of HIV infection will be undertaken using Mann-Whitney U and chi-square tests to determine whether there has been a significant decline in new HIV infections during this 36-month period, compared to the 36 months prior to PrEPX commencing.

We will undertake further analyses to determine whether or not other factors such as an increase in background HIV and STI testing rates during the PrEPX study period and an increase in the background rate of HIV virological suppression of HIV positive people living in Victoria during the PrEPX study period may have contributed to any decrease in new HIV infections. These analyses will be undertaken using Cox proportional and logistic regression analyses to calculate hazard or rate ratios and odds ratios, respectively, with 95% confidence intervals. To determine the factors associated with incident HIV infection among trial participants, we will explore demographic and behavioral risk factors.

To answer the study secondary aims a range of datasets and analyses will be employed, as required. The enrolment survey, ACCESS behavioral survey, and ACCESS test data will be used to explore baseline demographics, behavior, HIV risk factors, prevalence of STIs and blood borne viruses among GBM presenting for PrEP, changes in behavior and STI rates among PrEP users and ancillary health benefits among PrEP users. The in-depth online survey and interviews will be used to explore attitudes to PrEP, reasons for taking PrEP and attitudes around sexual behavior since the availability of PrEP. We will use ACCESS test data, pharmacy data and in-depth online surveys to explore PrEP adherence. Monthly aggregate data from the state NPEP service will be descriptively analyzed to explore state wide use of clinic survey and ACCESS test data will be used to explore the capacity of study clinics to prescribe PrEP.

All statistical analyses will be performed using Stata version 14 (StataCorp LP, College Station, Texas, USA) with a significance cut off of *p* = 0.05.

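### The before/after comparison has no trend term and the case list starts only in 2013, so a PrEPX effect cannot be told apart from an existing trend and any projection of that trend is imprecise

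*Protocol article*

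**What the plan says.** The Protocol article (Methods, Other study data) describes the records to be obtained from the state health department. The scope of that request is fixed by these words: "age, and exposure to HIV for all newly diagnosed cases in Victoria between 2013-2019". The same section notes the completeness of the source: "It is a legal requirement that all newly diagnosed cases of HIV are notified to the DHHS".

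Statistical analyses says new infections will be followed "for a period of 36 months after the PrEPX study commences". The comparator is an equally long earlier window ("compared to the 36 months prior to PrEPX commencing"), and the methods named for the contrast are "Mann-Whitney U and chi-square tests to determine whether there has been a significant decline in new HIV infections during this 36-month period". The section adds further analyses of testing rates and virological suppression by Cox and logistic regression. It states no trend term for the notification counts.

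On dates, Registration and waitlist data collection says: "The study opened on 26 July 2016 and data collection among enrolled participants is scheduled until July 2019". On policy, Study setting says: "Since 2013, the PBS has provided ARVs to PLWH at any CD4 cell count".

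**The concern.** The study has no control group, so the earlier notifications are the only stand-in for what would have happened without PrEPX. Two features weaken that stand-in.

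- The named tests compare two blocks of time. A decline already under way would show as a difference between the blocks and could be credited to PrEPX.
- The list begins in the year treatment funding was extended to any CD4 count. It therefore holds little or nothing from before a change that could itself lower transmission gradually, and it limits how precisely a prior slope can be estimated.

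At stake is the primary aim, which names specific sizes: a 30% fall in gay and bisexual men (GBM) and 25% statewide. That aim needs an estimate against a credible projection as well as a significant difference between two periods.

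**Working it through.** **Inputs from the Protocol article.** Sample size estimates: "We estimated that there are 300 new HIV infections per year in Victoria", 75% of them in GBM, with 68 a year to be averted. Check: 300 × 0.75 = 225, and 68/225 = 30.2%, so the stated 30% reproduces. Monthly GBM count μ = 225/12 = 18.75. Target rate ratio 0.70, log 0.357 in size. Follow-up 36 months.

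**Prior months available.** The list gives years without months. If it starts on 1 January 2013, opening on 26 July 2016 leaves 42.8 months, about 43.

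**Assumptions not in the document.** Poisson counts, a log-linear prior trend, the full effect from opening, two-sided 5% level.

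**1. The planned contrast under a trend alone.** Suppose no PrEP effect and an existing fall of 5% a year. The windows' midpoints are 3 years apart, so the expected ratio is 0.95³ = 0.857. Expected counts are about 675 × 0.95^(−1.5) = 729 before and 675 × 0.95^(1.5) = 625 after. For the totals, z = (729 − 625)/√(729 + 625) = 2.8. Simulating Mann-Whitney on monthly counts gives significance in about 75% of trials. A fall of 11.2% a year would by itself produce a 30% drop (0.888³ = 0.70), and the test is then significant in about 100%.

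**2. Effect against the extrapolated prior trend.** With n prior months, projecting to the middle of follow-up:

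Var(log RR) = d²/(μS) + 1/(μn) + 1/(0.7 × μ × 36), where S = (n³ − n)/12 and d = n/2 + 18.

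- n = 36: S = 3,885, d = 36. Variance = 0.01779 + 0.00148 + 0.00212 = 0.02139.
- n = 43: S = 6,622, d = 39.5. Variance = 0.01257 + 0.00124 + 0.00212 = 0.01592.
- n = 84: S = 49,385, d = 60. Variance = 0.00389 + 0.00063 + 0.00212 = 0.00664.

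Interval = exp(−0.357 ± 1.96 SE). Power = Φ(0.357/SE − 1.96).

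| Prior months | SE | 95% interval | Power |
|---|---|---|---|
| 36 | 0.146 | 0.53 to 0.93 | 68% |
| 43 | 0.126 | 0.55 to 0.90 | 81% |
| 84, single slope | 0.081 | 0.60 to 0.82 | 99% |

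The slope term d²/(μS) dominates at 36 and 43 months. The 95% margin on the prior slope is about 8% a year with 36 months and 6.5% with 43.

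**3. The same 84 months with a term for the 2013 change**, placed 43 months before opening (assumed):

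| 2013 term | SE | Power |
|---|---|---|
| Level | 0.100 | 94% |
| Slope | 0.113 | 88% |
| Level and slope | 0.126 | 81% |

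With both terms the earlier months tell the model nothing about the later line, so the result equals the 43-month fit.

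**4. Other trend-aware models.** A step on a common linear trend has 85% power at 36 months and 90% at 43. A segmented model testing the level change at opening has 84% and 87%.

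**5. Sensitivity.** Assumed overdispersion of 1.5 to 2 lowers power for the projection model at 36 months to 51% and 41%.

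**The case against.** Four points can be made for the plan, and much of each stands.

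- **The list does not force a 36-month baseline.** A reader might infer that it does. It holds about 43 months if it starts in January 2013, and Statistical analyses chooses 36. Using all of them already lifts power from 68% to 81%.
- **The series is not too short under every model.** A reader might conclude that no trend-aware analysis could work. The counts do not support that: step models have 84 to 85% power at 36 months, and even the weakest case has an interval that excludes 1. These models answer narrower questions, though. The common-trend model assumes PrEPX leaves the slope unchanged, and the level-change model measures only the jump at opening.
- **Earlier years need not halve the uncertainty.** Going from 0.146 to 0.081 compares the shortest baseline with a single slope fitted straight across 2013. If the policy change altered both level and slope, the gain over the existing list is nil. Starting in 2013 also has merit, since it keeps the baseline under one treatment policy.
- **The article offers context and other checks.** The Introduction reports stable national notifications over four years. Sample size estimates cites stable testing, and the Discussion plans triangulation with surveillance-site data. These make a steep prior decline less likely. They do not establish the slope in Victoria, and they put no trend into the primary comparison.

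A fuller analysis plan may say more. The tests and both time windows are nevertheless stated here as the primary analysis.

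**Conclusion.** The concern holds in a limited form. The primary comparison, as stated, cannot distinguish a PrEPX effect from a continuing trend: a modest assumed decline of 5% a year makes it significant about three times in four with no effect at all. That is the main weakness, and more years of data would not cure it while those tests remain.

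The start of the list is the secondary weakness. A true 30% fall in GBM, judged against the projected prior trend, would be reported as a fall of between 7% and 47% with 36 prior months, or between 10% and 45% with 43. Either interval shows a decline; neither says closely whether about 30% was reached.

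These figures rest on 225 cases a year, Poisson variation, a log-linear trend and an immediate effect. Overdispersion would widen them. The documents do not show that Victorian notifications were actually falling before the study; the point is that the plan could not tell.

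**What to change.** 1. In Statistical analyses, keep the 36-versus-36 contrast as a description. Make the estimate of decline a segmented count model (Poisson with allowance for overdispersion) on monthly notifications. Use every pre-study month available and report the ratio to the projected trend with its 95% interval.
2. In Other study data, extend the request to about 2009, roughly 84 months before opening, with the same fields. Notification is mandatory and the department is the same.
3. Fix in advance how the 2013 treatment change enters the longer model (level, slope or both), because that choice decides the gain. Report the longer fit beside the fit from 2013 onward.

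The cost is one line in the data request and some extra analysis, with no added burden on participants. The downsides are that exposure coding in older records must be checked for consistency and that the longer series mixes treatment-policy eras. The SE improves from 0.126 to 0.100 with a level term and to 0.113 with a slope term. It does not improve if both are needed.

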### Sample size estimates

We estimated that there are 300 new HIV infections per year in Victoria based on back-calculation methods applied to surveillance data and a modeling framework. With high and stable testing rates and HIV notification trends in Australia, these estimates have demonstrated strong concordance with actual trends in new infections (1, 48, 49). Approximately 75% of new HIV infections in Victoria occur in GBM, providing an estimate that 225 new infections occur in GBM in Victoria, annually.

We powered the study to avert 68 new HIV infections annually among GBM, which equates to a 30% reduction in new HIV infections in GBM in Victoria. We consider that this would represent a meaningful population-level prevention outcome from scaling up PrEP. Power calculations were based on a HIV incidence estimate of 2.78 per 100 person years (PY) from high risk GBM (consistent with risk criteria guidelines for PrEP) in the Health in Men (HIM) cohort study (50). The HIM study measured HIV incidence among GBM in Sydney in the early-to-mid 2000s (50). There are not adequate, contemporary Victorian data to determine HIV infection risk for GBM, but participants in HIM were not dissimilar in characteristics nor in epidemiological context to GBM in Victoria and Wilson et. al. has shown that the per-capita transmission rate has remained relatively stable since that period (51). We estimated that the number of GBM at risk of HIV in Victoria was 28,846 (225/0.78 per 100PY). With an estimated 24% classified as high risk [as per the HIM study (50)] and hence targeted for study participation, our target population size was therefore estimated as 6,923 (28,846 × 0.24). We estimated that a sample size of 2,600 participants (37% of high risk GBM) was required to achieve the 30% annual HIV infection reduction outlined above. Achieving this PrEP coverage was considered feasible given recent survey data showing that 32% of GBM classified as having high HIV acquisition risk were both willing and eligible to use PrEP (37).

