## Introduction

In Australia, HIV is largely concentrated among gay, bisexual and other men who have sex with men (GBM). Almost three quarters of annual notifications are among men reporting male to male sex as their exposure to HIV, with other exposures such as injecting drug use, heterosexual sex and being born in a high prevalence country being less commonly reported (1). In 2015 there were 1025 new HIV diagnoses in Australia and there were an estimated 25,313 people living with HIV (PLWH) (estimated prevalence of 0.1%) (1, 2). Despite significant investment in, and uptake of, HIV prevention activities, the annual number of HIV notifications has remained stable over the last four years (1).

HIV pre-exposure prophylaxis (PrEP) is the newest tool in the HIV prevention toolkit. PrEP is the use of tenofovir and emtricitabine on a daily or on demand schedule to prevent HIV transmission (3, 4). There is substantial evidence of the safety, efficacy and effectiveness of PrEP at reducing HIV transmission in GBM, trans-women, heterosexual men and women and people who inject drugs (3, 5–11). The efficacy of PrEP is directly correlated with medication adherence (12, 13) with recent open label trials reporting high adherence and greater reduction in risk of HIV acquisition compared to earlier, blinded studies (13, 14). While PrEP is highly effective at reducing HIV transmission it confers no protective effect against sexually transmissible infections (STIs) with the exception of HSV2 infections (15, 16). Concerns have been raised that PrEP use would increase condomless peno-anal or peno-vaginal sex, number of sex partners and in turn incidence of STIs, however there is mixed evidence of such changes occurring (11, 14, 17). In 2015 the World Health Organisation recommended PrEP as an HIV prevention option for all key populations (18). As at November 2017, PrEP is approved for use by the regulatory authorities of at least 20 countries, including Australia. Although approximately 30 countries currently run or plan to implement PrEP demonstration projects (19), there are as yet no publications which confirm the population level impact of PrEP.

Australian PrEP guidelines are based on individuals' risk of HIV acquisition. PrEP is recommended for people reporting high or moderate risk for acquiring HIV through male to male sex, heterosexual sex, and/or injecting drug use. Recent changes to the guidelines also permit clinicians' discretionary prescription of PrEP (20).

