PrEPX planning	Sep-Dec 2015	Approached clinics and community pharmacies to participate in the PrEPX study. Approached peak organizations including VAC, LPV, VACCHO, Centre for Culture, Ethnicity and Health.
	29 Jan 2016	Funding announced by the Victorian DHHS, Alfred Health and VAC for 2,600 places in PrEPX study.
	30 Jan 2016	Study registration opened using REDCap on the Alfred hospital website. Data collected: name, contact details, preferred clinic to attend for PrEPX, whether participant was on PrEP.
	22 Jul 2016	2049 people registered interest on online formClinics provided with partially de-identified list from registration form to enable workforce planning when study openedRegistered individuals emailed about study opening dates and booking information for their preferred clinic.
PrEPX study period	26 Jul 2016	PrEPX enrolment began (wave one of study enrolment) 2600 places opened, 150 of these reserved for priority populations including people who inject drugs and/or people in serodiscordant heterosexual partnerships with high or medium risk for HIV acquisition as per PrEP prescribing guidelines (Table 2).
	14 Oct 2016	PrEPX study neared enrolment capacityStudy enrolment stopped at 2200 participants to allow for people who had booked an appointment and not yet attended to join the study, with other places reserved for priority populations.First waitlist was opened, pending further funding.
	17 Jan 2017	Additional 600 places in PrEPX announced, funded by VAC.
	19 Jan 2017	Additional places released (wave two of study enrolment)All 575 people registered on the waitlist were provided a study place. Clinics were provided a list of participants as per original PrEP enrolment.
	20 Jan 2017	Waitlist was reopened.
	28 Mar 2017	Additional 600 places announced, funded by Victorian DHHS.
	29 Mar 2017	Additional places released (wave three study enrolment)All 617 people registered on the waitlist were provided a study place Clinics were provided list of participants as per original PrEP enrolment.
	30 Mar 2017	Waitlist was reopenedWaitlist remains open November 27th 2017.
	30 June 2019	PrEP-X study estimated end date.

*VicPrEP, Victorian PrEP demonstration study; PrEPX, Victorian PrEP population level study; PrEPX-SA, expansion of PrEPX study to South Australia; VAC, Victorian AIDS Council, LPV, Living Positive Victoria; VACCHO, Victorian Aboriginal Community Controlled Health Organisation Inc.; DHHS, Department of Health and Human Services*.

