### Study participants

#### Inclusion criteria

Eligible participants must be HIV-negative at their baseline PrEPX appointment, aged 18 years and over, have an estimated glomerular filtration (eGFR) rate of >60 mL/min/ 1.73 m^2^ and meet the behavioral eligibility criteria of the 2015 ASHM PrEP Guidelines (42). Eligible participants are individuals reporting male to male sex, injecting drug use and/or serodiscordant heterosexual sex with high or medium risk for HIV acquisition (Table 2) (42). Individuals not meeting these behavioral eligibility criteria can be enrolled at the clinician's discretion, if the clinician is of the opinion that the patient would benefit from being on PrEP (Table 2).

**Table 2 T2:** Eligibility criteria for PrEPX Study.

	**Gay, bisexual and transgender people**	**Heterosexual and transgender people**	**People who inject drugs**
Predicted risk of the study participant in the next 3 months	Likely to have multiple events of condomless anal intercourse (CLAI), with or without sharing intravenous drug use equipment	Likely to have multiple events of condomless anal or vaginal intercourse, with or without sharing intravenous drug use equipment	Likely to have multiple events of sharing needles or injecting equipment with an HIV positive individual or a homosexually active man and has inadequate access to safe injecting equipment

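### At the protocol's own incidence, 2,600 places avert 68 GBM infections a year only at about 94-99.8% direct effectiveness, so the 30% is a near-best-case projection, not a powered effect

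*Protocol article*

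**What the plan says.** The protocol article, Sample size estimates, starts from the statewide burden ("We estimated that there are 300 new HIV infections per year in Victoria") and takes 75% of it as GBM, "providing an estimate that 225 new infections occur in GBM in Victoria, annually". It continues: "We powered the study to avert 68 new HIV infections annually among GBM", which it equates with a 30% reduction. The rate used is an "HIV incidence estimate of 2.78 per 100 person years (PY) from high risk GBM". The section concludes: "We estimated that a sample size of 2,600 participants (37% of high risk GBM) was required to achieve the 30% annual HIV infection reduction". It gives no effectiveness, adherence, retention or statistical power.

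Other sections bear on that figure:

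- Introduction: "The efficacy of PrEP is directly correlated with medication adherence".
- Table 1, on the first 2,600 places: "150 of these reserved for priority populations including people who inject drugs and/or people in serodiscordant heterosexual partnerships".
- Inclusion criteria: "Individuals not meeting these behavioral eligibility criteria can be enrolled at the" discretion of the clinician.
- Study aims ties 2,600 people to both a 30% fall among GBM and a 25% statewide fall. Statistical analyses repeats 2,600 with the 30% target.
- Abstract, Study funding and Discussion give 3,800 participants, and the Abstract attaches the same 25% and 30% targets to that larger number.

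**The concern.** The section presents 2,600 as the number required for a 30% fall and describes the study as powered for it. The inputs it prints are an incidence, a population and a coverage. Multiplied together, they leave almost no room between the infections that 2,600 people would have had and the infections to be averted. The article itself says that efficacy follows adherence, reserves places for groups that may not be GBM, and admits people outside the criteria to which the 2.78 rate belongs.

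The 30% and 25% figures are the study's stated targets. If they sit at or beyond the most that direct protection could deliver, PrEP could work as expected, the observed fall could miss the target, and the result could be misread as a population-level failure.

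**Working it through.** **Inputs.** From Sample size estimates: 300 infections a year; 225 in GBM; target 68; 2.78 per 100 person-years; 0.78 per 100 person-years overall; 24% high risk; 2,600 participants. From Table 1: 150 reserved places. From Study funding: 3,800 places. From Study aims: 25% statewide.

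**Reproducing the plan's steps.**
- 0.75 × 300 = 225; 0.30 × 225 = 67.5, printed as 68; 68/225 = 30.2%.
- 225/0.0078 = 28,846; 28,846 × 0.24 = 6,923; 2,600/6,923 = 37.6%, printed as 37%.
- The last step, N = 68/(0.0278 × effectiveness), gives 2,446 at 100% and 2,602 at 94%. So 2,600 is recovered only with an unprinted factor of about 94%.

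**Direct protection at full enrolment.** Infections without PrEP = N × 0.0278. The needed factor, effectiveness × retention, is the target divided by that number.

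| High-risk GBM in places | Infections/year without PrEP | Maximum GBM decline | Factor needed for 68 |
|---|---|---|---|
| 2,600 | 72.28 | 32.1% | 94.1% |
| 2,450 (2,600 − 150) | 68.11 | 30.3% | 99.8% |
| 3,800 | 105.64 | 47.0% | 64.4% |
| 3,650 (3,800 − 150) | 101.47 | 45.1% | 67.0% |

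The unrounded target of 67.5 lowers the first factor only to 93.4%.

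**Statewide aim.** 0.25 × 300 = 75.
- With 2,600 places all at 2.78, the maximum is 72.28/300 = 24.1%, and the needed factor is 75/72.28 = 103.8%.
- If the 150 reserved places are non-GBM, they would have to supply 75 − 68.11 = 6.89 infections a year, a rate of 6.89/150 = 4.6 per 100 person-years, even with perfect protection throughout. The article gives no rate for that group.
- With 3,800 places, the needed factor is 75/105.64 = 71.0%.

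**Illustrative ranges.** The article states no combined effectiveness × retention; 70-90% is assumed here.
- 2,600 places, GBM: from 2,450 × 0.0278 × 0.70/225 = 21.2% to 2,600 × 0.0278 × 0.90/225 = 28.9%.
- 2,600 places, statewide, all at 2.78: 50.6/300 = 16.9% to 65.1/300 = 21.7%.
- 3,800 places, GBM: from 3,650 × 0.0278 × 0.70/225 = 31.6% to 3,800 × 0.0278 × 0.90/225 = 42.3%.
- 3,800 places, statewide, all at 2.78: 73.9/300 = 24.6% to 95.1/300 = 31.7%.

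**Detectability, as a separate question.** Treat the GBM totals as Poisson counts over 36 months before and after, with baseline 3 × 225 = 675, two-sided 0.05 and z = (a − b)/√(a + b).
- 15% fall: (675 − 573.75)/√1,248.75 = 2.87; power = Φ(2.87 − 1.96), about 82%.
- 30% fall: (675 − 472.5)/√1,147.5 = 5.98; power over 99%.

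This approximation stands in for the tests named in Statistical analyses and assumes no underlying trend.

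**The case against.** The strongest reply is that the study now plans 3,800 places, for which 64-67% suffices. That stands for the study as enrolled, provided the added enrolees carry the same 2.78 rate. It does not settle the text, because Study aims, Sample size estimates and Statistical analyses still pair the targets with 2,600.

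A second reply is that an article may leave its effectiveness assumption to the full protocol. That also stands, and the missing input alone would be no finding. But the printed figures close only with a near-perfect hidden value for GBM, and at 2.78 they do not close at all for the statewide aim.

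A third is that some allowance may exist: 2,600 − 2,446 = 154, which could reflect 94% effectiveness or roughly the 150 reserved places. The article does not say which, and the margin cannot cover both in full.

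Several stronger readings are tempting and are not supported:

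- A reader might infer that 30% is unreachable with 2,600. The arithmetic counts direct protection only. Onward infections prevented could add to it, although the article neither invokes nor quantifies them. The direct ceiling is 30.3-32.1%, slightly above 30%.
- A reader might infer that everyone must be protected from the first day. The target is annual and needs only full enrolment. Ramp-up matters for the 36-month comparison. As an illustration, assume 2,200 enrol evenly to 14 October 2016, 400 more by 19 January 2017, and none drop out. That gives about 7,413 person-years to late July 2019 and 7,413 × 0.0278 = 206 averted at 100%, against 3 × 68 = 204.
- A reader might infer that the study is underpowered or has no test. Statistical analyses names tests and a 0.05 cut-off, and a fall well short of 30% would probably be detected.
- The 99.8% is an extreme case. The list of priority groups is not exhaustive, and people who inject drugs may also be GBM.
- The article does not show that adherence will be poor. The Introduction cites high adherence in recent open-label trials, and the Rationale reports it for the predecessor study.

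**Conclusion.** The point holds for the 2,600-person design to which the aims and analysis still refer. On the article's own inputs, the 30% GBM target needs about 94% effectiveness × retention in every place, and up to 99.8% if no reserved place goes to GBM. The 25% statewide target lies above the direct maximum of 24.1%. The calculation is coverage multiplied by incidence; the planned tests and significance level play no part in arriving at 2,600. The weakness is whether the stated effect can be reached, not whether it could be detected.

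The conclusion rests on direct protection only, the 2.78 rate applying to every place counted, and full enrolment. People enrolled at lower risk would raise the needed factor; onward-transmission benefit would lower it. At 3,800 places the targets are attainable at about 64-67% (GBM) and 71% (statewide). This is a should-fix matter of how the targets are derived and described.

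**What to change.** 1. In Sample size estimates, call the paragraph an impact projection and drop the language of power.
2. State the assumed effectiveness × retention, the GBM share of places, and how enrolees outside the risk criteria are treated.
3. Give the projected GBM and statewide declines as ranges for both 2,600 and 3,800. For 2,600, the GBM range is, for example, 21-29% at an assumed 70-90%.
4. Reconcile 2,600 with 3,800 in the Abstract, Study aims, Sample size estimates and Statistical analyses, so that each target belongs to one stated size.
5. Report separately the decline that the before/after comparison can detect.
6. If onward-transmission benefit is relied on to reach 30% or 25%, say so and quantify it.

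The cost is rewriting and a short table, with no extra participants or data. The downside is that the stated effect for 2,600 becomes less favourable.
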